## Abstract

**Background:**

Progress of cholangitis to cholangiosepsis is a frequent observation in patients with secondary sclerosing cholangitis in critically ill patients (SSC–CIP). Adequate biliary drainage may reduce episodes of cholangiosepsis and therefore stabilize liver function and improve survival. The primary objective of the BISCIT study is to demonstrate that scheduled biliary interventions will reduce incidence of cholangiosepsis, liver transplantation, or death in patients with SSC–CIP.

**Methods:**

A total of 104 patients will be randomized at ten study sites. Patients with SSC–CIP, confirmed by endoscopic retrograde cholangiography (ERC), will be randomized 1:1 either in the intervention group which will be treated with scheduled biliary interventions (i.e., therapeutic ERC) every 8 weeks for 6 months or in the control group which will receive standard of care. The randomization will be stratified by center. The composite primary efficacy endpoint is defined as (1) occurrence of death, (2) necessity of liver transplantation, or (3) occurrence of cholangiosepsis within 6 months following randomization.

**Discussion:**

Prospective evaluation of endoscopic treatment procedures is urgently needed to establish an evidence-based therapeutic treatment algorithm in SSC–CIP. A positive trial result could change the current standard of care for patients with SSC–CIP. The results of this study will be disseminated through presentations at international congresses, workshops, and peer-reviewed publications.

**Trial registration:**

The trial was registered at ClinicalTrials.gov (NCT05396755, date of registration: May 31, 2022, last update: May 31, 2022).

## Trial status

The current version of the study protocol described in the manuscript is Version 1.0, February 23, 2022. The trial was registered at ClinicalTrials.gov (NCT05396755, date of registration: May 31, 2022, last update: May 31, 2022). No patient has yet been recruited. Approximate end of recruitment will be May 2025.

## Introduction

### Background and rationale

Secondary sclerosing cholangitis (SSC) is a condition characterized by progressive destruction of the biliary tree caused by a wide variety of stimuli including but not limited to toxic and infectious agents, immune-mediated mechanisms, and ischemia [1]. Recently, a new sub-entity of SSC has been defined in critically ill patients (SSC–CIP). SSC–CIP occurs weeks or months after the onset of a very broad range of critical conditions that include but are not limited to major trauma, burns, major thoracic or abdominal surgery, sepsis/septic shock, and the acute respiratory distress syndrome (ARDS) [2–5]. SSC–CIP frequently leads to recurrent acute cholangitis and cholangiosepsis, cirrhosis, hepatic decompensation, and ultimately death. Prognosis of SSC–CIP is dismal with an estimated survival of less than 50% of patients who develop SSC–CIP within 3–6 months [2–4]. Other publications estimate a 1-year survival of 55% and only 14% after 6 years [5]. Current understanding and management of SSC–CIP are based on a limited number of reports with small patient numbers [2–5]. The exact pathological mechanisms and clinical risk factors have not been elucidated conclusively. A number of trigger factors have been proposed as causes for the development of SSC–CIP, including prolonged hypotension, vasopressors administration, intensive mechanical ventilation, and prone positioning [6].

Therapeutic approaches for patients with SSC–CIP include endoscopic interventions via endoscopic retrograde cholangiography (ERC) with sphincterotomy, removal of biliary casts, flushing of the bile ducts, dilation therapy, stent placement, and placement of nasobiliary drainages [2–5]. Patients with clinical evidence of bacterial cholangitis are treated with broad spectrum antibiotics according to microbiologic testing if available [5]. Ursodeoxycholic acid (UDCA) administration has been suggested, although data on effectiveness are lacking [7]. In case of end-stage disease, liver transplantation is a therapeutic option in selected patients [8].

To date, efficacy of endoscopic interventions has not been proven and an evidence-based standard therapy for SSC–CIP remains to be defined. Programmed (e.g., repeated) ERC interventions are intended to improve biliary drainage, reduce episodes of cholangitis, prevent biliary cirrhosis, and preserve liver function. However, ERC interventions including sphincterotomy and insertion of different catheters and guide wires into the biliary system might on the contrary even be harmful by promoting bacterial cholangitis, hence further accelerating disease progression.

### Objectives

The objective of this trial is to clarify whether endoscopic interventions in patients with SSC–CIP are beneficial or if an alternative, then conservative strategy, should be rather preferred. Consequently, our results will have a strong impact on the clinical management of patients with SSC–CIP.

### Trial design

This is a multicenter, randomized, controlled parallel group trial. Patients with confirmed SSC–CIP will be randomized 1:1 either in the intervention group which will undergo scheduled invasive evaluation of the biliary tract with ERC with biliary interventions (i.e., therapeutic ERC) every 8 weeks for 6 months or in the control group which will receive non-interventional standard of care (SOC) (Fig. 1). The primary endpoint is a composite endpoint consisting of the individual components cholangiosepsis, liver transplantation, and death (whatever occurs first). Study participants will be followed up to 12 months following study inclusion. This study is an investigator-initiated trial funded by the German Research Foundation (DFG, VO 2458/1–1).

**Fig. 1 Fig1:**
[figure not shown]
Trial structure

## Methods

### Participants, interventions, and outcomes

#### Study setting

A total of 104 patients with SSC–CIP (1:1 randomization) will be included in up to ten study centers in Germany. The study is currently planned at the following centers in Germany (BISCIT study group): Hannover Medical School, Department of Gastroenterology, Hepatology and Endocrinology; Charite University Medicine Berlin, Clinic for Gastroenterology and Hepatology; University Hospital Freiburg, Clinic for Gastroenterology, Hepatology, Endocrinology and Infectious Diseases; University Hospital Magdeburg, Clinic for Gastroenterology, Hepatology and Infectious Diseases, Magdeburg, Germany; Hospital Nuernberg, Department of Gastroenterology and Endocrinology; Sana Hospital Offenbach, Department of Gastroenterology, Gastro-oncology and Interventional Endoscopy, Offenbach, Germany; University Hospital Regensburg, Department of Gastroenterology, Endocrinology, Infectious Diseases and Rheumatology; University Hospital Munich (LMU), Department of Gastroenterology and Hepatology.

#### Eligibility criteria

Patients have to fulfill all of the following inclusion criteria to be eligible for participation in the study:Men, women*, inter/divers, age ≥ 18 and ≤ 80 years (conscious or unconscious patients may be included)Signed written informed consent obtained by patient or legal representative in case of unconscious patientWillingness to comply with treatment and follow-up proceduresSuspected SSC–CIP = episode of critical illness and intensive care unit treatment > 3 days within last 12 monthsSSC–CIP is confirmed by ERC (if the first ERC is performed at baseline, the patient may be considered as screening failure if the diagnosis is not confirmed (see below))Elevation of bilirubin ≥ 2.5 upper limit of normal (ULN) at screeningElevation of alkaline phosphatase (AP) or gamma-glutamyl-transferase (GGT) > 2.5 ULN or elevation of both at screeningWomen without childbearing potential defined as follows:

At least 6 weeks after surgical sterilization by bilateral tubal ligation or bilateral oophorectomy orHysterectomy or uterine agenesis or≥ 50 years and in postmenopausal state > 1 year or< 50 years and in postmenopausal state > 1 year with serum follicle-stimulating hormone (FSH) > 40 IU/l and serum estrogen < 30 ng/l or a negative estrogen test, both at screening

or

Women of childbearing potential:

Who are practicing sexual abstinence (periodic abstinence and withdrawal are not acceptable) orWho have sexual relationships with female partners only and/or with sterile male partners orWho are sexually active with fertile male partner, have a negative pregnancy test during screening, and agree to use reliable methods of contraception (failure rate of < 1% per year) from the time of screening until end of the clinical trial.

Patients are excluded from participation in the trial if they meet one of the exclusion criteria:Patient is too unstable to undergo ERCInclusion in any other intervention trial within the last 30 daysPregnancy or lactation period

#### Who will take informed consent

Patients (conscious or unconscious) with suspected SSC–CIP are considered for inclusion in this trial. The investigator is responsible for obtaining patient’s/legal representative’s written informed consent after adequate explanation of the aim, study assessments, potential risks and benefits, and consequences of the study as well as alternative treatment options. If patients are incapable of giving consent due to unconsciousness, informed consent may be given by a legal representative who has been designated by the local court. After retrieval of capacity for informed consent, patients have to be informed about study-specific interventions that have already been done and about the treatments that are planned in the future. Patients have to be asked if they want to continue participation in the trial and have to sign an informed consent form themselves. The patient information/informed consent form has to be signed in duplicate by the patient/legal representative and the investigator. One document will be given to the patient/legal representative; the other one remains in the trial investigator file (TIF) at the trial site. No study procedures are allowed to be conducted until patient’s/legal representative written informed consent has been obtained. The patient information/informed consent form has to be revised whenever important new information becomes available that may be relevant to the subject’s consent. The patients have to be informed and asked to give their consent to continue study participation by signing the updated form. Participation in this clinical trial is voluntary. Withdrawal from the trial at any time and for any reason is without any disadvantages to the patient’s further treatment.

#### Interventions

Patients with SSC–CIP are randomized either to the interventional or control arm. Patients in the experimental group will undergo scheduled invasive evaluation of the biliary tract with ERC and endoscopic interventions every 8 weeks until 6 months (24 weeks). Patients in the SOC group will receive only non-interventional standard of care treatment. Patients in both arms will be followed up every 8 weeks with clinical and laboratory assessment (Table 2). After 6 months (24 weeks), both groups are followed up every 8 weeks until 12 months.

Endoscopic evaluation has to be performed at baseline in both groups and during each ERC in the intervention group. Furthermore, an assessment of the biliary tract has to be made in each patient during V1 after diagnosis of SSC and before randomization to intervention group or control arm. Contrast injection with ERC catheter after attempt of bile extraction will be used in both groups. In the control arm, the procedure is terminated after contrast injection. They will be managed using a strictly conservative strategy that avoids biliary interventions unless such intervention is unequivocally mandated by the clinical situation. We foresee that this will be the case only in cholangiosepsis with obstruction which is part of the composite endpoint. Patients in the control arm will be seen every 8 weeks and a blood collection with acquisition of clinical data will be performed. After 6 months, a control MRCP will be performed in both groups in order to evaluate and compare the extent of bile duct damage between the groups. In the intervention group potential endoscopic interventions are as follows: sphincterotomy (V1-4), occlusion cholangiogram (V1-V4), extraction of all removable biliary casts via balloon, brush, basket and/or flushing (V1-V4), dilatation or bougienage of all endoscopically treatable bile duct stenoses (V1-V4), largest size of balloon or bougienage in relation to bile duct size has to be applied (V1-V4). Selective intubation of ductus hepaticus sinister and dexter with visualization and balloon cleaning is preferred (V1-V4). At the end of the procedure, flushing of the left and right biliary system with 20 ml Ringer’s lactate solution in order to flush remnants of contrast medium (V1-V4) and stent placement at physician’s assessment V1-V4 (high-grade stenosis of the bile ducts with insufficient dilatation or bougienage) will be performed. After the ERC, the following items have to be documented: procedure time, the extracted material (stones, cast, sludge and/or pus), largest size of balloon or bougienage if used, the possibly applied stent(s) and the potential use of intra-biliary antibiotics, flushing catheters or nasobiliary drainage (V1-4).

A bile specimen of up to 5 ml will be collected at baseline and visit 2 to visit 4 (only intervention-group) to analyze the microbial microenvironment in the biliary system and bile to gain insights in its role during SSC–CIP. Moreover, blood samples per visit of approx. 15 ml (serum/plasma) and 2.6 ml (genetic analysis, only screening) will be obtained for the evaluation of the exploratory endpoints.

#### Outcomes

##### Primary endpoint

The primary endpoint (Table 1) is the failure rate defined as a composite endpoint consisting of:Occurrence of death orNecessity of liver transplantation orOccurrence of cholangiosepsis (defined by SEPSIS-3 criteria and diagnosis of acute cholangitis according to the Tokyo Guidelines), whatever occurs first

**Table 1 Tab1:** Endpoints

**Primary endpoint**	Composite endpoint of: Cholangiosepsis (acute cholangitis (Tokyo criteria) and sepsis (Sepsis-3 criteria) Liver transplantation Death (whatever occurs first)
**Secondary endpoints**	
Single components of the primary endpoint	Cholangiosepsis Liver transplantation Death
Laboratory parameters	Bilirubin, alkaline phosphatase (AP), gamma-glutamyl transferase (GGT), aspartate aminotransferase (AST), alanine aminotransferase (ALT), lactate dehydrogenase (LDH), glutamate dehydrogenase (GLDH), creatinine, C-reactive protein (CRP), cholinesterase (CHE) as change from baseline
Model for end-stage liver disease score (MELD)	MELD as change from baseline
Unplanned hospital admissions	Necessity and days free of hospital care within 6 months
Unplanned intensive care unit (ICU) admissions	Necessity and days free of intensive care unit care, invasive ventilation, renal replacement therapy, vasopressors within 6 months
Necessity of anti-infective treatment	
**Safety endpoints**	
Death	
Liver transplantation	
Cholangiosepsis	
Cholangiosepsis-associated septic shock	
Acute on chronic liver failure (ACLF)	ACLF of any grade
Unexpected in-patient hospitalization or prolongation of existing hospitalization	
Unexpected ICU hospitalization	
ERC-related SAEs	Acute post ERC cholangiosepsis, acute post ERC pancreatitis, post ERC bleeding originating from the biliary system, duodenal or biliary perforation, aspiration pneumonia, allergic reaction to sedation associated with endoscopic procedure
Other SAEs	Other potentially life-threatening events as assessed by the individual investigator

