##### Safety endpoints

A serious adverse event (SAE) is defined as any event that is potentially life threatening and may or may not be associated with the procedure under investigation. In detail, all following events are categorized as SAEs (Table 1):DeathLiver transplantationCholangiosepsisCholangiosepsis-associated septic shockAcute on chronic liver failure (ACLF) of any gradeUnexpected in-patient hospitalization or prolongation of existing hospitalizationUnexpected ICU hospitalizationERC related SAEsOther potentially life-threatening events as assessed by the individual investigator

SAEs will be collected throughout the study and documented in the eCRF and on an SAE-form. The assessment of possible serious adverse events takes place by the investigator from inclusion of subjects into the study until the end of follow-up. SAEs including a risk–benefit evaluation of the study by the responsible investigator will be reported periodically (every 3 months) to the Ethics Committee according to the Declaration of Helsinki.

Given the profound severity of disease in the patients under investigation (hospitalized patients, mostly under critical care, multiple clinical, and laboratory abnormalities), adverse events (AEs), not fulfilling the definition of a SAEs (see above), will not be reported in this study.

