**Clinical assessment**						
Informed consent	x					
Eligibility criteria	x					
Gender and age	x					
Medical history	x					
ICU related history	x					
Vital signs and oxygen saturation	x	x	x	x	x	x
Height and skin color	x					
Weight	x	x	x	x	x	x
Concomitant medication	x	x	x	x	x	x
Pregnancy prevention counseling	x	x	x	x	x	
Endoscopic evaluation (ERC)		x	x (intervention group)	x (intervention group)	x (intervention group or clinically necessary for UN/ET)	
MRCP^b^	x				x	
Endoscopic intervention (ERC)		x (endoscopic evaluation only at non-intervention group)	x (intervention group)	x (intervention group)	x (intervention group or clinically necessary for UN/ET)	
Randomization		x				
Checking the components of the primary endpoint^c^			x	x	x	x
Secondary endpoints^d^					x	
SOFA score		x	x	x	x	x
Serious adverse events		x	x	x	x	x

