#### Sample size

The primary aim of the study is to demonstrate superiority of the experimental group compared to the control group in patients with SSC–CIP. The primary endpoint is a failure rate defined as a composite endpoint including liver transplantation, death, or cholangiosepsis after 6 months. Sample size calculation was conducted using a two-group continuity corrected chi-square test in nQuery Advisor 7.0. The type I error is set to 5% (two-sided) and the study aims for a power of 80%. In the present trial, a rate of 70% regarding the composite endpoint is expected in the control group. This assumption is based on the following observations: prognosis of SSC–CIP is dismal with an estimated survival of less than 50% of patients who develop SSC–CIP within 3–6 months [2, 4, 7]. The transplant-free survival of SSC–CIP differs between publications. However, in our large cohort, transplant-free survival was 38.9% at 6 months [9, 16]. Additionally, biliary complications in SSC–CIP are numerous affecting up to 90% of patients [6]. Cholangiosepsis accounts for 20–33% of these biliary complications [6]. A total reduction of 30% is assumed for sample size calculation. This number is estimated from clinical observation and experience of patients with SSC–CIP and PSC [11]. To demonstrate a reduction of the rate from 70 to 40% in the experimental group, a sample size of 49 patients per group is needed leading to *n* = 98 in total. The expected drop-out rate is assumed to be 5% (estimation from clinical practice), which leads to a sample size of 52 patients per study arm and 104 patients in total.

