#### Analysis of safety endpoints

Occurrence of complications and adverse and serious adverse events will be analyzed descriptively using absolute and relative frequencies for the whole population and separately for the experimental and control groups and will be compared with chi-squared tests.

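### Table 1 counts a post-ERC bleed as ERC-related only if its source is biliary, so duodenal bleeds fall outside the row and sphincterotomy-site bleeds are unclear

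*Protocol article*

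**What the plan says.** In the Protocol article, Table 1 (Safety endpoints) gives the content of the ERC-related SAE row as a list of named complications. Two neighbouring items read "post ERC bleeding originating from the biliary system, duodenal or biliary perforation". The list is closed: nothing marks the items as examples. The text section on safety endpoints only names ERC-related SAEs as a category and refers back to Table 1.

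The section Interventions puts "sphincterotomy (V1-4), occlusion cholangiogram (V1-V4" first among the possible procedures in the experimental arm. For controls it says "In the control arm, the procedure is terminated after contrast injection", followed by a conservative strategy that "avoids biliary interventions unless such intervention is unequivocally mandated by the clinical situation". Table 2 agrees, with the entry "endoscopic evaluation only at non-intervention group" for the baseline visit.

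The text section on safety endpoints defines an SAE broadly, as "any event that is potentially life threatening and may or may not be associated with the procedure under investigation". Under Analysis of safety endpoints, event frequencies are reported for the whole population and "separately for the experimental and control groups and will be compared with chi-squared tests".

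**The concern.** The ERC-related row is the only place in the safety table that isolates harm caused by the procedure. Its bleeding item is narrower than the perforation item beside it, and narrower than the article's own Discussion, which names bleeding as a complication of ERC without limiting the site.

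Sphincterotomy is a cut at the papilla, where the bile duct meets the duodenum. One center may call a bleed from that cut biliary and another may call it duodenal. With up to ten centers, the same event could be filed in different rows.

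Therapeutic ERC is given almost wholly in one arm, so bleeds filed elsewhere would make the row understate procedural harm mainly in the experimental arm. The trial asks whether repeated intervention helps or whether a conservative approach is preferable, so the row that carries the procedural cost should be counted consistently.

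**Working it through.** **Reading the text.** The question is mainly one of wording, so the relevant places are set side by side.

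| Place in the Protocol article | Bleeding | Perforation |
|---|---|---|
| Table 1, ERC-related SAEs | biliary source only | duodenal or biliary |
| Safety endpoints (text) | category named only, refers to Table 1 | same |
| Discussion | named as an ERC complication, no site limit | not named |

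1. Within one table cell the article treats the duodenum and the biliary system as separate sites. A bleed from the duodenum is therefore not a biliary bleed in the article's own terms, and it falls outside the row.
2. Could the word for the duodenum belong to bleeding instead? The comma comes before it and the noun that follows is perforation, so that reading is strained.
3. No other section widens the bleeding item or places a papillary bleed on either side.
4. A serious bleed outside the item remains reportable. It can enter through unexpected or prolonged hospitalization, ICU stay, death or the catch-all row for other SAEs. None of these rows attributes the event to ERC.

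**Exposure by arm.** The arm size comes from Sample size: "which leads to a sample size of 52 patients per study arm and 104 patients in total". That figure reproduces. Rates of 70% and 40%, two-sided 5% alpha, 80% power and a continuity-corrected chi-square test give 49 per group. Then 49 / (1 − 0.05) = 51.6, rounded up to 52, and 2 × 52 = 104. The visits come from Interventions and Table 2.

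- Experimental arm: 52 patients × 4 scheduled therapeutic ERCs (V1, V2, V3, V4) = 208 at most, fewer after death, transplantation or discontinuation. Sphincterotomy is a possible part of each, so 208 is not a count of sphincterotomies.
- Control arm: 52 × 1 diagnostic ERC at V1 = 52 at most, and 0 scheduled therapeutic ERCs. Rescue ERCs are possible, but the article does not give their number.

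**Weight of one refiled patient.** If a patient's only ERC-related event is a bleed filed in another row, the experimental arm's ERC-related rate falls by 1/52 = 0.0192, or 1.9 percentage points. This takes the denominator as the planned 52. The safety population is analyzed as treated, so the actual denominator may differ slightly.

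The article gives neither a bleeding rate nor a split by site. No expected number of refiled bleeds is derived, and none is assumed.

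**The case against.** The strongest reply is that nothing is lost. The SAE definition is broad, other rows catch a serious bleed, and in a randomized trial the comparison of all SAEs by arm shows excess harm whatever the row label. This is true and limits the point to attribution.

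Second, an endoscopist would probably file a bleed from a sphincterotomy as biliary. The article calls the experimental treatment biliary intervention and lists sphincterotomy under it, and the Discussion shows no wish to exclude such bleeds. This is fair for the papilla, and on that reading few events are affected. It does not reach bleeding from the duodenum, which the wording still leaves out.

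Third, a journal article condenses a full protocol, and the SAE form, which is not shown, may settle the coding. The form could resolve the papilla. For the duodenum, however, Table 1 states a limit and does not merely omit a detail. A form that counted duodenal bleeds would contradict it.

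Fourth, a relatedness judgement by investigators who know the allocation brings in subjectivity that a purely anatomical rule avoids. That is a real cost, but a small one, because the row is already headed as ERC-related and so already implies such a judgement.

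Finally, the exposure figures are not counts of misfiled bleeds. That is correct, and they are used here only to show in which arm an undercount would fall.

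**Conclusion.** The point holds and is minor. As worded, Table 1 leaves serious duodenal bleeding after ERC outside the ERC-related row and does not place sphincterotomy-site bleeding. Any resulting undercount would fall mainly on the experimental arm, at 1.9 percentage points per patient refiled.

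The total size is unknown and may be near zero. It depends on how often such bleeds occur, whether sites treat the papilla as biliary, and what the SAE form says. The primary endpoint, sample size, type I error, all-SAE comparison and periodic risk-benefit evaluation are not affected.

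**What to change.** Reword the item in Table 1 as: post-ERC bleeding judged related to the procedure, from the papilla or sphincterotomy site, the duodenum or the biliary system. State that it applies to every ERC in both arms, including rescue ERC in controls. The relatedness condition keeps unrelated gastrointestinal bleeding in critically ill patients out of the row.

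The cost is one line in Table 1, the matching line on the SAE form and one relatedness judgement per bleed. Serious bleeds are already reportable as SAEs, so the extra data collection is slight. The reported ERC complication rate may come out slightly higher.
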